### Example of individualized preventive care recommendations

To better understand the study, Fig. 2 provides an example of the decision tool that will be seen by a patient and provider. At top is an individualized statement; e.g., “You are 60 years old but have the health of a 69 year old.” Below, a bar graph shows the improvement if a patient utilizes all recommended preventive (and chronic disease management) services and that associated with each service, as previously described [20].

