**Select tertiary/exploratory**		
To assess reach	% of eligible patients for whom provider accesses individualized recommendations	None
To assess adoption	% of providers approached by the study team who agree to enroll; patient self-rating of: how helpful s/he found the recommendations, how interested s/he is in seeing individualized recommendations again in the future	None
To assess implementation	Adaptations made to intervention; known issues with fidelity	None
To assess maintenance	Provider reach at quarterly intervals post-enrollment; helpfulness of individualized recommendations 6 months after enrollment, self-reported by patient survey.	None

This table shows primary, secondary, and select tertiary/exploratory study endpoints. See the study protocol for all tertiary/exploratory endpoints

^a^ In patients of intervention arm providers, as compared with patients of control arm providers

^b^ “Top-” (“bottom-”) ranked individualized preventive care recommendations are defined as follows: top (bottom) 3 for patients with ≥6 recommendations, 2 for patients with 4–5 recommendations, 1 for patients with 3 recommendations, not applicable for patients with ≤2 recommendations. Only collected for preventive services that a patient states his/her provider discussed during the baseline encounter

^c^ Assessed for the subgroup of patients recommended each service. Only considered when follow-up data are available for ≥30 high patients of intervention arm providers and ≥30 patients of control arm providers

Because an increase in QALE may be difficult to achieve, we will assess a number of important secondary outcomes. Disease prevention is a complex process, requiring behavior change at the patient, provider, health system, and state/national levels. We will learn whether the tool promoted desirable changes for preventive care and chronic disease management: comprehension of the tool, use of shared decision-making, and readiness to change. If comprehension and/or shared decision-making are high, then even if patients do not ultimately change their preventive care (or chronic disease management), they better understand their health care needs, resulting in a more informed decision. If readiness to change is high, then the tool may have helped patients want to utilize preventive (or chronic disease management) services, but additional interventions are needed to improve adherence and QALE.

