#### Patients

Eligible patients will have the following inclusion criteria:Aged 40–75 years.A modifiable lifestyle factor with a large impact on QALE, assessed by ≥1 of the following: current smoker, body mass index (BMI) ≥30.0 kg/m^2^, BP ≥140/90 mmHg, 10-year atherosclerotic cardiovascular disease (ASCVD) risk ≥10%, glycated hemoglobin (HbA1c) ≥9% or alcohol consumption/week of >7 drinks (4.2 oz) for females or >14 drinks (8.4 oz) for males. Our rationale is that ≥1 individualized recommendation should have a high magnitude of impact on quality-adjusted life expectancy. Consistent with primary prevention, alcohol misuse will focus on asymptomatic excess; e.g., 2–3 drinks most nights without dependency.Eligible for a high number of preventive services, assessed by ≥3 of the following: current smoker, BMI ≥27.0 kg/m^2^﻿, systolic BP >130 mmHg, 10-year ASCVD risk ≥7.5%, HbA1c ≥7.5%, alcohol consumption/week of >7 drinks (4.2 oz) for females or >14 drinks (8.4 oz) for males, overdue/due soon for colorectal cancer screening, overdue/due soon for lung cancer screening, overdue for ≥1 year for breast cancer screening, overdue for ≥1 year for osteoporosis screening. Our rationale is that patients with a high number of individualized recommendations may have greater need for prioritization, as compared with other patients.Ongoing primary care in the health system, defined as ≥2 in-person or virtual visits with a primary care provider (PCP) in the prior 730 days. Our rationale is that follow-up EHR data are more likely to exist for patients with ongoing primary care, as compared with other patients.Annual wellness visit or closely related encounter (e.g., hypertension follow-up) with the patient’s PCP of record. Virtual visits are eligible, although in-person visits may be preferable.

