### Intervention

Patients decide which preventive (and chronic disease management) services to pursue in complex environments, influenced by the desire to improve their health and other factors (e.g., personal obligations at work or at home) that affect feasibility. By better understanding which preventive (and chronic disease management) services are most likely to promote a longer, healthier life, we hypothesize that patients can improve their health outcomes.

Figure 3 describes the study’s conceptual framework, guided by the heterogeneity of treatment effect (HTE) model [33–35]. HTE addresses variation in a study’s results across individual patients, who, based on their individual risk factors, derive different benefit from an intervention. Few patients receive the “average” treatment effect. Patients at high-risk benefit more, while those at low-risk may not benefit at all. Here, we quantify the net benefits of various preventive and chronic disease management interventions for individual patients based on their evidence-based risk factors. We convert these to a single metric, the change in QALE from utilizing each service, and rank-order the results. This contrasts with a current process of clinical guidelines developed for *populations* of patients. Next, a provider will discuss the individualized recommendations with a patient. Rather than a sequential approach (e.g., hypertension control, then glycemic control, then breast cancer screening), we will ask providers to engage in a holistic conversation about all of a patient’s primary prevention (and chronic disease management) needs utilizing shared decision-making. A patient has *options* to improve his/her health, none of which is required, but all of which would be beneficial. The patient must decide which service(s) to pursue, based on our model and external factors: effort (e.g., lifestyle changes are difficult); available time in the context of work, family, hobbies; personal preferences; attitudes/beliefs; cost; trust in the provider and health system; and other medical needs not addressed by our intervention. We hypothesize that patient outcomes will improve if providers help patients understand which preventive (and chronic disease management) services are most likely to improve their QALE, and discuss them using shared decision-making, as compared with current processes. Below, we describe the intervention in detail.

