### Statistical analysis

The biostatistician will conduct analyses based on an equivalence design, with a modified intention-to-treat (ITT) patient population. Each patient who completed the baseline primary care encounter (excluding no shows, cancellations, etc.) and his/her provider will be treated in the group according to initial randomization. Linear mixed-effect models with random intercepts at the patient and provider levels will be used. Such models assume data missing at random. Sensitivity analyses may consider full ITT and per protocol populations, as well as multiple imputation for missing data. Full ITT is not expected to yield significant results because approx. 1/3 of primary care patients do not show up or cancel scheduled encounters [20]. Subgroup analyses will be by race. There are no planned interim analyses.

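### The article adopts a risk-based heterogeneity-of-effect framework but names race as its only effect subgroup and prespecifies no analysis by baseline attainable QALE gain

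*Protocol article*

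**What the plan says.** The Intervention section that introduces the conceptual framework (Fig. 3) says the framework is "guided by the heterogeneity of treatment effect (HTE) model". It explains the term: "HTE addresses variation in a study’s results across individual patients, who, based on their individual risk factors, derive different benefit from an intervention". It adds a direction: "Patients at high-risk benefit more, while those at low-risk may not benefit at all". It then turns to the tool: "we quantify the net benefits of various preventive and chronic disease management interventions for individual patients based on their evidence-based risk factors".

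The Statistical analysis section plans linear mixed models with random intercepts for patient and provider. It names no baseline-risk term and gives one subgroup factor: "Subgroup analyses will be by race".

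The only other subgroup wording is Table 3, footnote c, on the service-specific secondary endpoints: "Assessed for the subgroup of patients recommended each service".

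The tool already displays a patient-level total: "a bar graph shows the improvement if a patient utilizes all recommended preventive (and chronic disease management) services". According to the section on collection of study endpoints, model inputs come from an EHR feed for every patient from the baseline encounter onwards.

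**The concern.** The framework says that benefit varies with risk. The one named effect subgroup, race, is among the model's many inputs and does not measure how much a patient has to gain. The closest single measure is the modelled QALE gain from taking up all recommended services. The article does not say that this will be used, either as a covariate or as an effect modifier.

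Two things are at stake. An analysis by attainable gain that is first specified after results are known would carry the usual doubt about post hoc selection. The primary comparison may also give up precision if attainable gain predicts QALE change.

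**Working it through.** **Setting the passages side by side.** The Intervention section describes variation in results by individual risk. The Statistical analysis section gives an average arm effect plus race. Table 3, footnote c does not bridge the two: it fixes the denominator for each service-specific secondary endpoint, does not compare effects across levels of gain, and does not concern the primary outcome.

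**Inputs from the Power section.** 60 providers with 10 patients each (300 patients per arm), ICC 0.01, difference 3.0 months, power 86.2%. Sensitivity case: 54 providers, ICC 0.02, power 80.4%. The article gives neither SD nor alpha, so 86.2% cannot be reproduced from its own inputs. I assume two-sided alpha 0.05 and solve for the SD.

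**Step 1, implied SD.** Design effect = 1 + (10 − 1) × 0.01 = 1.09. SE = SD × √(2 × 1.09/300). Power = Φ(3/SE − 1.96) = 0.862 gives SD ≈ 11.54 and SE ≈ 0.984 months.

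**Step 2, check against the sensitivity case.** Design effect 1.18, 270 per arm: SE = 11.54 × √(2 × 1.18/270) ≈ 1.079, so power = Φ(3/1.079 − 1.96) ≈ 79.4%, against the stated 80.4%. A one-sided alpha of 0.05 would imply an SD of about 12.9 and predict 80.2%. The two stated figures agree well enough to use the implied SD.

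**Step 3, interaction with attainable gain split in two.** For a fraction f in one group, SE = 0.984 × √(1/f + 1/(1 − f)).

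| Split | Power for a 3-month difference in effect | Detectable difference at 80% power |
|---|---|---|
| 50/50 (SE ≈ 1.97) | 33% | 5.5 months |
| 33/67 | 30% | 5.9 months |
| 25/75 | 26% | 6.4 months |

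Treating the 50/50 contrast as within-provider (factor 0.99 in place of 1.09) raises 33% to 36%.

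**Step 4, interaction as a slope.** Per SD of baseline gain, SE = 2 × 11.54/√600 ≈ 0.942. The detectable slope at 80% power is 2.80 × 0.942 ≈ 2.6 months per SD, or about 2.8 with 540 patients.

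**Step 5, as a covariate.** If baseline gain explains a share R² of the variance in QALE change, SE becomes 0.984 × √(1 − R²). The article gives no R²; the range is an assumption.

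| Assumed R² | Power for 3.0 months |
|---|---|
| 0 | 86.2% |
| 0.1 | 89.5% |
| 0.2 | 92.6% |
| 0.3 | 95.4% |

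**The case against.** A reader might infer that the trial leaves its own hypothesis untested. The article does not support that. The sentence about high-risk patients belongs to a general account of the framework, which is then applied mainly to individualise service benefits inside the tool. The stated hypotheses, in the Abstract and Table 3, are average effects between arms. This part of the objection stands.

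A reader might also infer that the trial cannot say who benefits more. That is too strong, because model inputs exist for every patient and the analysis can be run. What is absent is a stated prespecification, and the unseen full protocol or SAP may contain one.

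Entry criteria narrow the range of gain. Patients need at least one high-impact factor ("Our rationale is that ≥1 individualized recommendation should have a high magnitude of impact on quality-adjusted life expectancy") and at least three indicators from a longer list. A narrower range leaves less for an interaction to show.

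The proposed variable has two weaknesses. The article says diet and physical activity are little recorded in the EHR, and the baseline survey that would supply them follows the encounter, so a pre-encounter value captures those services poorly. Attainable gain and the outcome also come from the same model: the same change in behaviour yields more QALE in a higher-risk patient by construction. Both points stand and limit how the slope may be read.

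The framework passage nevertheless speaks of variation in a study's results, and attainable gain addresses that more directly than race does.

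**Conclusion.** The point holds as a gap between framework and stated analysis: race is the only effect subgroup the article names, and no analysis by baseline attainable QALE gain is prespecified there. It is a low-priority improvement.

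The interaction would estimate heterogeneity more than test it. The detectable slope of about 2.6 months per SD is close to the whole 3.0-month target effect. These sizes rest on the assumed two-sided alpha of 0.05 and the back-solved SD of about 11.5 months.

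Power of about 90–95% for the primary comparison might be read as a promised gain. It applies only if R² lies between 0.1 and 0.3, which nothing in the article establishes.

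**What to change.** Unless the full protocol or SAP already does so:

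- Define baseline attainable QALE gain as the modelled gain from all recommended services, computed in both arms from EHR inputs dated before the baseline encounter.
- Enter it as a continuous covariate in the primary mixed model.
- Prespecify its interaction with arm as an exploratory analysis, reported as a slope with a confidence interval and not as a median split.
- Keep race as a further subgroup.
- State the limits beside the analysis: low power for the interaction, poor pre-encounter capture of diet and physical activity, a slope that describes absolute benefit and not differential response to the tool, and a precision gain that depends on an unknown R².

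The cost is two model terms and a short definition. No new data are collected, and a covariate fixed before the encounter should not bias the primary estimate.

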### Power

A sample size of 60 providers (30/arm), each with 10 patients, will have 86.2% power to detect a clinically meaningful 3.0-month difference in the change of QALE between the 2 arms. We assume a small intra-cluster correlation coefficient (ICC)=0.01 because life expectancies of different patients are unlikely to be correlated, even from the same provider. In sensitivity analysis, estimated power is 80.4% for a sample size of 54 providers and an ICC=0.02. Therefore, the study will still have adequate power if 10% of patients are lost to follow-up, consistent with our pilot study [20].

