**Methods:**

The Personalized Disease Prevention (PDP) cluster-randomized clinical trial will evaluate whether patients and their providers benefit from an evidence-based decision tool to prioritize preventive services based on their potential to improve quality-adjusted life expectancy. The decision tool will be individualized for patient risk factors and available in the electronic health record. This Phase III trial seeks to enroll 60 primary care providers (clusters) and 600 patients aged 40–75 years. Half of providers will be assigned to an intervention to utilize the decision tool with approximately 10 patients each, and half will be assigned to usual care. Mixed-methods follow-up will include collection of preventive care utilization from electronic health records, patient and physician surveys, and qualitative interviews. We hypothesize that quality-adjusted life expectancy will increase by more in patients who receive the intervention, as compared with controls.

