#### Patients

Through automated data feeds from the EHR linked with upcoming appointment schedules, and manual chart review as needed, the study team will identify specific patients. We will ask if the patient’s provider is willing to discuss individualized recommendations with this patient. The team will seek to enroll the patient and remind providers shortly before the scheduled encounter.

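### The powered number and the enrolment target are both 600, but enrolment precedes the visit and the primary analysis drops non-attenders: the article must say which count the 600 is

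*Protocol article*

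**What the plan says.** Four statements in the protocol article bear on this point.

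- **Target.** The Abstract (Methods) says the trial "seeks to enroll 60 primary care providers (clusters) and 600 patients".
- **Timing.** Under Intervention, Patients: "The team will seek to enroll the patient and remind providers shortly before the scheduled encounter".
- **Analysis set.** Statistical analysis defines the primary population as modified intention-to-treat, limited to patients who completed the baseline encounter. No-shows and cancellations are excluded. In explaining why full intention-to-treat is not expected to give significant results, it adds that "approx. 1/3 of primary care patients do not show up or cancel scheduled encounters".
- **Power.** "A sample size of 60 providers (30/arm), each with 10 patients, will have 86.2% power" for a "clinically meaningful 3.0-month difference in the change of QALE between the 2 arms". The text continues "We assume a small intra-cluster correlation coefficient (ICC)=0.01" and, as sensitivity analysis, "estimated power is 80.4% for a sample size of 54 providers and an ICC=0.02". From this it concludes that power remains adequate with 10% of patients lost to follow-up. The reason given for the small ICC is that "life expectancies of different patients are unlikely to be correlated, even from the same provider".

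**The concern.** The number used for power and the number to be enrolled are the same, 600. Between enrolment and analysis, however, the plan has a filter, attendance at the baseline visit, and the article itself puts the failure rate at about one-third. The 10% allowance in the Power section is for loss to follow-up. That is a different loss: a patient who never attends does not enter the modified intention-to-treat set at all.

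If recruitment stops at 600 enrolled, the stated 86.2% is not the power of the specified primary analysis, and the assurance of adequate power after 10% loss fails. If recruitment is meant to continue until 600 have attended, the power statement is sound but the enrolment target understates the recruitment needed.

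A smaller point concerns the ICC. Its rationale is about life-expectancy levels, which may well be unrelated between patients of one provider. The outcome is the change in QALE, and in the intervention arm that change is meant to come partly from how the provider uses the tool.

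**Working it through.** **Inputs from the article:** 60 providers, 10 patients each, difference 3.0 months, ICC 0.01 (sensitivity 0.02), power 86.2%, non-attendance about 1/3, loss to follow-up 10%.

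**Inputs assumed:** two-sided 5% test of a difference, normal approximation. The article gives neither alpha nor the SD, so 86.2% cannot be reproduced independently; the SD is solved from it.

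**Formulae:** design effect DE = 1 + (m − 1) × ICC; effective number per arm n = (60 × m / 2) / DE; SE = SD × √(2/n); power ≈ Φ(3.0/SE − 1.960).

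**Step 1, SD implied by 86.2%.** DE = 1 + 9 × 0.01 = 1.09; n = 300/1.09 = 275.2. Power of 86.2% needs 3.0/SE = 1.960 + 1.089 = 3.049, so SE = 0.984 and SD = 0.984/√(2/275.2) = 11.54 months.

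**Step 2, check against the second stated figure.** With SD 11.54, 54 × 10 at ICC 0.02 gives 79.4%, against 80.4% stated. A one-sided 5% test, with its own back-solved SD, gives 80.2%. The article's two power figures therefore agree to about a point, provided all 10 patients per provider are analysed.

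**Step 3, the 600 counted at enrolment, non-attenders not replaced.** With one-third lost, m = 10 × 2/3 = 6.67 and the total is 400. At ICC 0.01, DE = 1 + 5.67 × 0.01 = 1.057, n = 200/1.057 = 189.3, SE = 11.54 × √(2/189.3) = 1.186, and power = Φ(2.529 − 1.960) = 71.5%. The other rows follow in the same way.

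| Analysed | Patients per provider | Power, ICC 0.01 | Power, ICC 0.02 |
|---|---|---|---|
| 600 | 10 | 86.2% | 83.4% |
| 480 (20% non-attendance, assumed) | 8 | 78.6% | 76.0% |
| 400 (one-third non-attendance) | 6.67 | 71.5% | 69.3% |
| 360 (one-third, then 10% loss) | 6 | 67.2% | 65.2% |

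The 480 and 400 rows are before loss to follow-up and compare directly with 86.2%. The 360 row adds that loss.

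**Step 4, sensitivity to alpha (SD re-solved each time).** At 400 analysed, one-sided 5% gives 73.3% and 71.4% (ICC 0.01 and 0.02), and two-sided 2.5% gives 69.9% and 67.4%. At 360 the figures are 69.6% and 67.9%, and 65.1% and 62.8%. Replacing the normal approximation by a t test on 58 degrees of freedom changes the two-sided 5% figures at 400 and 360 by no more than about 0.1 point.

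**Step 5, the 10 per provider counted as attenders.** Power stays at 86.2%. Enrolment before the visit then has to be 600/(2/3) = 900 at the stated rate.

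**The case against.** The strongest reply is that the 10 per provider are already attenders. The sentence after the enrolment target in the Abstract says intervention providers will use the tool with about 10 patients each, and a provider can use it only with someone who comes. The Power section follows directly on the definition of the modified intention-to-treat set. The authors plainly knew about non-attendance and kept it apart from loss to follow-up. On that reading 86.2% is right. This is a fair reading, and it is why the fall in power can only be stated conditionally. It does not remove the point, because the target is then expressed as patients to enrol, before a visit that about one-third are said to miss.

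Second, the one-third rate is given for primary care patients generally. Trial patients need at least two primary care visits in the prior 730 days, and the team contacts them ahead of the encounter, so their rate may be lower. This stands as a caution. Even at an assumed 20%, though, power would be about 76–79% before loss to follow-up.

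Third, a condensed article may leave replacement rules to the full protocol. That is true of the procedure. But the article itself gives the target, the analysis set, the non-attendance rate and the power, and these do not fit together as printed.

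Two stronger readings should be resisted. A reader might infer that the trial will have only about 400 analysed patients; nothing in the article says that the 600 are counted before attendance or that non-attenders are not replaced. A reader might also infer that the power calculation is wrong in itself; step 2 shows that its two figures agree. Representing the 10% loss as 54 providers rather than 9 patients per provider makes no material difference: 79.4% against 80.1% at ICC 0.02.

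**Conclusion.** The point holds as an inconsistency between the enrolment target, the analysis set and the power statement, with a conditional consequence. If the 600 are enrolled patients and non-attenders are not replaced, power for 3.0 months is about 69–72% instead of 86.2%, and about 65–67% after a further 10% loss. If the 600 are attenders, the power stands and about 900 is the enrolment figure at the stated rate. Either the power or the enrolment target therefore needs correcting.

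The power figures rest on a test of difference at two-sided 5%, an SD of about 11.5 months that the article does not state, and the general one-third rate applying to trial patients. The other alphas tried move them by roughly two or three points.

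The ICC rationale is a minor matter. The article already tests 0.02, which with a full 600 costs about three points (86.2% to 83.4%), and it gives no basis for a particular higher value.

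**What to change.** Define the 10 per provider and the total of 600 as patients who completed the baseline encounter. Say that invitations continue until each provider reaches that count, and give the expected enrolment separately (about 900 at one-third non-attendance, or the figure for whatever rate is expected in reminded trial patients). If recruitment will instead stop at 600 enrolled, restate the power for the expected modified intention-to-treat size, before and after 10% loss to follow-up. In either case, state the SD and alpha behind 86.2%, and reword the ICC justification so that it concerns change in QALE.

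The cost is a few sentences. Under the first option no analysed patients are added beyond those the power calculation already assumes, though more must be approached and enrolled. Under the second the cost is a less favourable stated power.
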